## Multivariate analysis

We will do multilevel multivariate analysis to compare the two care conditions controlling for baseline imbalance and clustering effects within practices on number of incident diagnoses (goal 1), quality of care (goal 2) patient and caregiver outcomes (goal 3). Effect modification will be explored on principal characteristics (age, gender, severity dementia and type of caregiver). A post hoc analysis on main outcomes will be done on patients who score under critical cut off on CAMCOG at baseline (<86).

In addition, an economic evaluation is performed from societal perspective comparing the effects of goals 1 to 3 and costs in the two conditions. To compare costs between the two groups, confidence intervals for the differences in mean costs are calculated using bias-corrected and accelerated bootstrapping with 5000 replications. For the cost-effectiveness analysis the difference in total costs between the intervention and usual care group are compared with the difference in main clinical outcomes.

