**Appendix 3. Overview of caregiver and patient outcomes and potential effect modifiers**

| *OVERVIEW* | Instrument | Items | Form | Time min | T0 | T1 | T2 | T3 | T4 |
| --- | --- | --- | --- | --- | --- | --- | --- | --- | --- |
| *Outcomes caregiver* |  |  |  |  |  | 6 m | 12m | 18m | 24m |
| Burden | SSCQ | 12 | I | 10 | X | X | X | X | X |
| QoL | MDS* & EQ5D |  | Q | 20 | X | X | X | X | X |
| Psychopathology | GHQ12 | 12 | I | 10 | X |  | X |  | X |
| Care utilisation, care time and absenteeism | MDSe* / cost diary |  | Q/I | 15 | X | X | X | X | X |
| *Outcomes pt* |  |  |  |  |  |  |  |  |  |
| Presence of dementia / MCI | CAMCOG1 |  | I | 25 | X |  | X |  |  |
| QoL | QoL-AD & EQ5D | 16 | I | 15 | X | X | X | X | X |
| Care utilisation etc. | MDSe* / cost diary by porxy |  | Q/I | 0 | X | X | X | X | X |
| Time until nursing home admission | According to carer or PCP | - | I |  |  |  | X |  | X |
| *Potential effect-modifiers / confounders* |  |  |  |  |  |  |  |  |  |
| Carer: |  |  |  |  |  |  |  |  |  |
| Sociodemography | MDS | 5 | I |  | X |  |  |  |  |
| Social support  Duration and intensity of caring | SSSL  Added Q | 8  1  1 | Q  I |  | X  X |  | X |  | X |
| Patient: |  |  |  |  |  |  |  |  |  |
| Sociodemography | By proxy | 5 | I | 5 | X |  |  |  |  |
| Dementia type | Medical Records | 1 | I | 0 |  |  | X |  |  |
| Morbidity | MDS by proxy | 1 | I | 5 | X |  |  |  |  |
| Behavioural symptoms | NPI | 12 | I | 10 | X |  | X |  | X |
| PCP / primary care practice:  - Age  - Sex  - Presence of practice nurse for elderly patients  - Interested in dementia  - % patients ≥ 65  - Cluster size | Q  Q  Added Q  Added Q  Medical rec | 1  1  1  3 | Q  Q  Q  Q |  | X  X  X  X  X  X |  |  |  |  |

I=Interview

Q=Questionnaire

MDS* / MDSe*: Minimal DataSet / Minimal DataSet cost-effectiveness respectively (NPO-ZonMW).

1 intervention arm only

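### The cost comparison names no baseline covariate, although care use is collected at T0 in both arms, so it gives up precision and carries over part of any chance imbalance in prior costs

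*Protocol*

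**What the plan says.** Section 9.3 (Multivariate analysis) holds two separate plans.

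- The clinical goals get a multilevel analysis, "controlling for baseline imbalance and clustering effects within practices on number of incident diagnoses (goal 1), quality of care (goal 2) patient and caregiver outcomes". Costs are not on that list.
- The economic evaluation follows as an additional analysis. For costs, "confidence intervals for the differences in mean costs are calculated using bias-corrected and accelerated bootstrapping with 5000 replications". For cost-effectiveness, "the difference in total costs between the intervention and usual care group are compared with the difference in main clinical outcomes". Neither sentence names a covariate, a regression, a T0 value or the practice as a unit.

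Appendix 3 marks care use at T0 for both members of the pair: for the caregiver, "Care utilisation, care time and absenteeism | MDSe* / cost diary | | Q/I | 15 | X"; for the patient, "Care utilisation etc. | MDSe* / cost diary by porxy | | Q/I | 0 | X". Its footnote "1 intervention arm only" is attached to the CAMCOG row only. Figure 2 shows 8 practices per arm, with baseline patient and caregiver measures in 156 per arm. Section 7.2 stratifies practices on existing collaboration with a practice nurse and on the share of elderly patients. Prior care use is not a stratification factor.

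**The concern.** Baseline care use is a natural covariate for later costs, and the plan already collects it. Followed as written, section 9.3 would lead an analyst to adjust the clinical outcomes and leave costs unadjusted. Sixteen practices are few, and they can differ by chance in prior home care, admissions or informal care. Part of such a difference would then appear in the cost contrast, and the interval would be wider than it needs to be.

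Cost-effectiveness is one of the secondary objectives in section 2, and the evidence base is thin by the protocol's own account: under its secondary endpoints, section 7.1 reports no cost-effectiveness information for this kind of intervention. Adding the covariate only after an imbalance has been seen would look data-driven, so it is better fixed beforehand.

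**Working it through.** **Inputs from the protocol.** 8 practices per arm (Figure 2); 156 patients per arm (Figure 2, section 4.4), so 156 / 8 = 19.5 per practice. The plan gives no figure for the cost analysis. Its 156 reproduces from the caregiver calculation in section 4.4: 57 / 0.5 / 0.80 × 1.10 = 156.75.

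**Assumed inputs, not in the documents.** ICC of costs within practices 0.01, 0.05, 0.10. Correlation r between baseline and follow-up costs 0.3, 0.5, 0.7, taken as equal at patient and practice level.

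**Step 1: chance imbalance at baseline.** Design effect = 1 + (19.5 − 1) × ICC. SD of the between-arm difference, in patient-level SDs = √(2 × design effect / 156).

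**Step 2: carry-over.** The expected shift in an unadjusted follow-up difference is r × the baseline difference. Its 95% limit is 1.96 × r × the SD from step 1.

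| ICC | Design effect | SD of baseline difference | Chance of a difference above 0.2 SD | 95% limit of carry-over at r = 0.3 / 0.5 / 0.7 (SD) |
|---|---|---|---|---|
| 0.01 | 1.19 | 0.12 | 10% | 0.07 / 0.12 / 0.17 |
| 0.05 | 1.93 | 0.16 | 20% | 0.09 / 0.15 / 0.22 |
| 0.10 | 2.85 | 0.19 | 30% | 0.11 / 0.19 / 0.26 |

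The plan's own 10% allowance for clustering (design effect 1.1) gives √(2 × 1.1 / 156) = 0.12 SD.

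**Step 3: precision.** The standard error after adjustment, relative to before, is √(1 − r²) = 0.954 / 0.866 / 0.714. That is a cut of about 5 / 13 / 29% (variance 9 / 25 / 49%). Under the assumptions above, this ratio does not depend on the sample size or the ICC.

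**Step 4: simulation check.** 8 v 8 practices of 20 patients, ICC 0.05, no true effect, normally distributed costs, 4000 runs per correlation.

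| r | SD of estimate, unadjusted | SD, adjusted | Slope on baseline difference, unadjusted | Slope, adjusted |
|---|---|---|---|---|
| 0.3 | 0.157 | 0.149 | 0.33 | 0.03 |
| 0.5 | 0.154 | 0.135 | 0.48 | −0.02 |
| 0.7 | 0.158 | 0.111 | 0.72 | 0.02 |

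The mean unadjusted estimate lay within 0.006 SD of zero, so there is no bias on average. Carry-over follows r, and adjustment removes it.

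**Step 5: clustering in the bootstrap.** If patients rather than practices were resampled, the standard error would be 1 / √(design effect) = 0.92 / 0.72 / 0.59 of the clustered one at ICC 0.01 / 0.05 / 0.10. A covariate alone would leave that interval too narrow.

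**The case against.** The protocol never calls the cost difference unadjusted. BCa is a way to form an interval and can be applied to a regression-adjusted difference. Appendix 3 lists care use among the caregiver and patient outcomes, so it could be read as falling under goal 3. Covariates for a secondary economic analysis are often left to the SAP. In addition, at r = 0.5 a one-SD baseline imbalance shifts the result by only half a standard error, which a valid interval already covers.

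Much of this stands. A reader might infer four stronger things that the documents do not support:

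- That the text prescribes an unadjusted comparison. It is silent, and the absence of adjustment is inferred. Still, research question 3 concerns wellbeing, information needs and worry, and costs have their own sentence, detailed down to the number of replications. An analyst following it has no instruction to adjust.
- That the cost result is biased, or that imbalance enters in full. Steps 2 and 4 show neither.
- That a baseline-adjusted effect is set against an unadjusted cost. The cost-effectiveness sentence does not say which estimate of the clinical difference is used.
- That the error can be put in euros. There is no cost SD to do so.

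Two further limits apply. The documents give no recall period for the T0 measure, so its predictive strength is unknown. Costs also rest on diaries kept by caregivers, so fewer than 156 per arm may be analysable. That would enlarge the chance imbalance but leave the percentages in step 3 unchanged.

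**Conclusion.** The point holds as a weakness of a stated method in a secondary analysis. Section 9.3 names no baseline covariate for costs, while Appendix 3 provides one in both arms. What is lost is precision, together with accuracy conditional on an observed imbalance; unbiasedness under randomisation is not in question. The standard error would fall by about 5 / 13 / 29% at correlations of 0.3 / 0.5 / 0.7. At ICC 0.05, the carried-over part has a 95% limit of 0.09 / 0.15 / 0.22 SD. All these sizes rest on assumed correlations and ICCs and on 156 patients per arm. The same sentence also leaves clustering by practice unmentioned for costs, and the repair has to deal with both.

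**What to change.** In section 9.3, state that:

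- the cost difference is the arm coefficient from a regression of total costs on arm and T0 costs, refitted in each bootstrap resample, with the BCa interval taken on that coefficient;
- resampling is by practice, or the model contains a practice effect, so that the interval respects clustering;
- in the same resample, the effect difference is adjusted for its own T0 value where one exists (for example EQ-5D, QoL-AD, GHQ-12, quality indicators). Incident diagnoses have no T0 value and are not adjusted in this way.

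If adjustment was always intended, this wording simply records it. The cost is a short addition to section 9.3 and slightly more analysis work. No new data are needed.

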## Interim analysis (if applicable)

Not applicable

# ETHICAL CONSIDERATIONS

## Regulation statement

<*In this section it can be stated that the study will be conducted according to the principles of the Declaration of Helsinki (version, date, see for the most recent version: www.wma.net) and in accordance with the Medical Research Involving Human Subjects Act (WMO) and other guidelines, regulations and Acts (if applicable, please specify)*>

## Recruitment and consent

Please see chapter 7.3 Study procedures.

## Objection by minors or incapacitated subjects (if applicable)

Not applicable

## Benefits and risks assessment, group relatedness

<*Please give a justification of the proposed study.*>

## Compensation for injury

The sponsor/investigator has a liability insurance which is in accordance with article 7, subsection 6 of the WMO.

The sponsor (also) has an insurance which is in accordance with the legal requirements in the Netherlands (Article 7 WMO and the Measure regarding Compulsory Insurance for Clinical Research in Humans of 23th June 2003). This insurance provides cover for damage to research subjects through injury or death caused by the study.

1. € 450.000,-- (i.e. four hundred and fifty thousand Euro) for death or injury for each subject who participates in the Research;
2. € 3.500.000,-- (i.e. three million five hundred thousand Euro) for death or injury for all subjects who participate in the Research;
3. € 5.000.000,-- (i.e. five million Euro) for the total damage incurred by the organisation for all damage disclosed by scientific research for the Sponsor as ‘verrichter’ in the meaning of said Act in each year of insurance coverage.

The insurance applies to the damage that becomes apparent during the study or within 4 years after the end of the study.

## Incentives (if applicable)

FPs get accreditation points for their participation in the training. The practice nurse is initially paid out of study resources. The goal is to increasingly draw on normal primary care resources (health insurance etc.) in the course of the project.

# ADMINISTRATIVE ASPECTS AND PUBLICATION

## Handling and storage of data and documents

All data is gathered either at the PCPs or at subjects’ homes (interviews/questionnaires). Data is transported on USB-sticks only. Coded data files may also be send by email. Data is stored on a hard disk of the research institute that is only accessible for authorised persons (only members of the research team are authorised) with a username and password. All data will be coded. Coding will be based on village, PCP, FP and a random number for subjects. There is no relation with initials or birth-date. Data will be stored for no longer than 115 years. The key to the code will be safeguarded by the principal investigator ([name]).

## Amendments

Amendments are changes made to the research after a favourable opinion by the accredited METC has been given. All amendments will be notified to the METC that gave a favourable opinion.

## Annual progress report

The sponsor/investigator will submit a summary of the progress of the trial to the accredited METC once a year. Information will be provided on the date of inclusion of the first subject, numbers of subjects included and numbers of subjects that have completed the trial, serious adverse events/ serious adverse reactions, other problems, and amendments.

## End of study report

The investigator will notify the accredited METC of the end of the study within a period of 8 weeks. The end of the study is defined as the last patient’s last visit.

In case the study is ended prematurely, the investigator will notify the accredited METC, including the reasons for the premature termination.

 Within one year after the end of the study, the investigator/sponsor will submit a final study report with the results of the study, including any publications/abstracts of the study, to the accredited METC.

## Public disclosure and publication policy

<*Please mention the arrangements made between the sponsor and the investigator concerning the public disclosure and publication of the research data. >*

# Appendices

**Appendix 1. Overview intervention**

**Possible cognitive impairment**

Screening PN

Consultation FP

**Dementia or MCI suspected?**

RAI Contact Assessment

MMSE, VAT, GDS, gehoor, visus.

b) Physical & neurological examination

c) Medication review

d) Diagnosis and disclosure

e) Diagnostic referral?

- Psychoeducation and support

- RAI Home Care if indicated by RAI Contact Assessment or if dementia

- Care plan

- Referral to services

**Yes**

**Revision care plan every 6 months or earlier when required**

**Dementia or MCI diagnosis?**

**Yes**

**No**

NHG-guideline recommendations:

a) Laboratory tests

Assessment and care PN

**Revision screening PN after 6 months**

**PN = practice nurse, RAI = Resident Assessment Instrument (comprehensive care needs assessment instrument) VAT = Visual Analogue Test, MMSE = Mini Mental State Examination, GDS = Geriatric Depression Scale**

**Appendix 2. overview of QIs, measured at baseline and at 12 months**

| **Process indicators (diagnosis)** |
| --- |
| 1. IF signs of dementia are noticed, THEN the general practitioner should start cognitive diagnostic workup within 3 months |
| 2. IF cognitive diagnostic workup has been started, THEN a ‘‘history from other sources’’ should be obtained. |
| 3. IF cognitive diagnostic workup has been started, THEN general physical examination should be conducted. |
| 4. IF cognitive diagnostic workup has been started, THEN neurological examination should be conducted. |
| 5. IF cognitive diagnostic workup has been started, THEN a blood test (at least erythrocyte  sedimentation rate, hemoglobin, mean corpuscular volume, creatinine, thyroidstimulating hormone, glucose) should be conducted. |
| 6. IF cognitive diagnostic workup has been started, THEN a cognitive screening test should be conducted. |
| 7. IF cognitive diagnostic workup has been started, THEN a mood screening test should be conducted. |
| 8. IF cognitive diagnostic workup has been started, THEN the patient’s physical, emotional and social needs should be assessed. |
| 9. IF cognitive diagnostic workup has been started, THEN the caregiver’s burden and needs should be assessed. |
| 10. IF a dementia diagnosis has been made, THEN it should meet the DSM-IV criteria.  1. Memory disorder  2. Other cognitive function disorder  3. Negative influence on daily functioning  4. Absence of a delirium |
| 11. IF a diagnosis has been made after cognitive diagnostic workup, THEN the general practitioner should disclose the diagnosis to patient and caregiver. |
| 12. IF a patient meets one of the following criteria, THEN the general practitioner should refer the patient to a multidisciplinary memory clinic.  1. Uncertainty about the diagnosis  2. Dementia diagnosis was made, and patients showed the following characteristics.  a. The course of the dementia was stepwise or rapidly progressive.  b. Characteristics that suggest rare types of dementia, like focal of frontal features or visual hallucinations in early stages of the dementia  c. Symptoms or results that suggest disorders that can only be treated by a specialist  d. Patient younger than 65  3. Patients or caregivers wish to start pharmacological treatment to ease dementia symptoms (cholinesterase inhibitors)  4. Patient’s or caregiver’s request to confirm the diagnosis |
| 13. IF a dementia diagnosis has been made, THEN the general practitioner should formally bring the cognitive evaluation to a close, reviewing the following items.  1. Explicit disclosure of the diagnosis  2. Information about the prognosis  3. Offering leaflets, written information on dementia  4. Suggestions on home care  5. Information on possibilities of cholinesterase inhibitor treatment in dementia  6. Driving abilities |
| **Process indicators (follow-up)** |
| 14. IF a dementia diagnosis has been made, THEN an individualized care plan for the patient should be formulated. |
| 15. IF a dementia diagnosis has been made, THEN an individualized care plan for the caregiver should be formulated. |
| 16. IF a dementia diagnosis has been made, THEN the care plan should be evaluated and if necessary updated every 3 months. |
| **Structure indicators** |
| 17. Cognitive diagnostic examination consists of at least two face-to-face consultations. |
| 18. The general practitioner is the first contact point or will delegate this task to the practice nurse. |
| 19. A guidebook, listing all social services for dementia patients and their caregivers, is available in the family practice. |
| 20. General practitioners and practice nurses use the same medical record. |
| **Outcome indicators** |
| 21. Continuity of care (indicators 16, 19, AND 21 complied with = 16, 18, 20?) |
| 22. Number of emergency consultations in dementia patients |
| 23. Satisfaction of the patient and the informal caregiver was assessed, using a validated questionnaire |

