**Main study parameters**

Ad 1-2 (b) 23 quality indicators: 13 on the diagnostic process, 3 on follow-up care, 4 on structure of care and 3 on outcomes after 12 months.

(a) The number of MCI and dementia diagnosis after 12 months.

Ad 3. Patient: Quality of life (EQ5D, QoL-AD); mental wellbeing (MH5); worrying (…), information needs (…). Caregiver: mental health (GHQ 12); burden (SSCQ); quality of life (EQ-5D); worrying (..), information needs (…) over 12 months.

Ad 4. Diagnostic accuracy of FPs’ cognitive classification of individuals compared to the reference standard (CAMCOG) diagnosis at baseline.

**Nature and extent of the burden and risks associated with participation, benefit and group relatedness:** The interventions done within the context of the study are regarded to be of no risk to the patients and caregivers exposed to them. We aimed to minimise the burden placed on dementia patients and their caregivers by limiting the interviews with patients and carers (and questionnaires for carers) to twice a year.

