## Sample size calculation

In order to come to a sample size that would allow showing significant differences in quality of care, in wellbeing and in numbers of new dementia diagnoses we performed several power calculations:

Quality of care:

The primary outcome is the difference in total score on a set of quality indicators (QIs) after 12 months between intervention and control group. Perry et al. found a mean (crosssectional) concordance to the total set of 45.3% (SD 30.4). A serial measurement is not yet done with this set of QIs.

For this study we expect an increase in concordance in the intervention group of around 1.5 times the baseline scores. In other words; an added 22,5% concordance with the total set of QIs is considered as clinically relevant. We based out powercalculation on the method described by Kerry et al.(Kerry and Bland 1998). To be safe we assumed a somewhat larger within cluster SD of 35 than Perry et al. found. Based on research of Campbell et al on ICCs in primary care research we assumed a between cluster SD of 3(Campbell et al. 2005).

With an α of 0.05 and β of 0.90, a sample size of 5 clusters per arm and 72 patients per arm is required to show a statistically significant and clinically relevant difference in quality of care.

Caregiver wellbeing:

We chose the GHQ12 as a meausure of caregiver mental health as the most important patient and caregiver wellbeing measure. We expect to find results after a period of 12 months on this outcome. We based our sample size for the GHQ 12 on a study of Diaz et al . in 2008. They report a significant difference in GHQ 12 decline between intervention and control group. The average difference in decline was 2.2 points in a period of 6 months. Based on their SDs we (conservatively) estimated SDs in the control- (4.3) and interventiongroup (3.6). Based on the formula: √(SDbaseline2 x SDfollow-up2).

A paired t-test for average difference with unequal variance shows that assuming an equal distribution over intervention and controlgroup,a desired power of 90%, and an alpha of 0.05 we need to include 57 caregivers per group in order to find significant and clinically relelvant results (SASsoftware). Estimating that about half of patients will have an informal caregiver and that about 20% will be lost to follow-up in the first year and adding 10 % for clustering resulted in a desired sample of 156 patients per arm.

Number of new dementia diagnoses in 12 months:

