### Main study parameter/endpoint

The primary outcome is quality of care: quality of the diagnostic process and subsequent care is measured by a set of 23 QIs (Perry et al. 2010). **Appendix 2** provides an overview of these QIs.

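### Two of the 23 indicators in the primary score, QI 21 and QI 22, have no usable scoring rule as written, and QI 16 is out of step with the intervention's default care-plan interval

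*Protocol*

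**What the plan says.** Protocol section 4.4 (Sample size calculation) fixes the endpoint: "The primary outcome is the difference in total score on a set of quality indicators (QIs) after 12 months". The same section expresses the score as percent concordance with the total set and takes 22.5 points as the relevant difference. Section 7.1 (Main study parameter/endpoint) says that "quality of the diagnostic process and subsequent care is measured by a set of 23 QIs" and refers to Appendix 2 for the list. The Summary gives the make-up: "23 quality indicators: 13 on the diagnostic process, 3 on follow-up care, 4 on structure of care and 3 on outcomes". Appendix 2 is therefore the definition of the primary endpoint.

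Three entries in Appendix 2 matter here:

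- QI 21: "Continuity of care (indicators 16, 19, AND 21 complied with = 16, 18, 20". The printed text ends in a question mark after the last number.
- QI 22: "Number of emergency consultations in dementia patients". Nothing further is stated.
- QI 16, once dementia has been diagnosed: "THEN the care plan should be evaluated and if necessary updated every 3 months".

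The intervention flow chart in Appendix 1 has: "Revision care plan every 6 months or earlier when required".

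**The concern.** A percent-concordance total needs each item to resolve to met, not met or not applicable. QI 21 depends on itself and carries an unanswered drafting query about which items belong in it. QI 22 is a number of events, and the appendix does not say what number counts as concordant, or whether fewer or more is better. Whoever computes the score has to make these decisions. If they are made after the data are seen, part of the primary contrast rests on a choice that was not fixed in advance.

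The choice for QI 21 may not be neutral between arms. QIs 18 and 20 concern delegation to the practice nurse and a shared record. Section 5.1 puts an extra nurse in every intervention practice and says that only a minority of usual-care practices have one for the elderly. QI 19, a guidebook of services, has no such link.

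The third issue is one of consistency. The trial scores care-plan evaluation at one interval and describes an intervention whose default revision interval is longer. Because QI 16 is a component of QI 21, the mismatch reaches two items.

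**Working it through.** **1. The plan's own count.** Appendix 2 lists QIs 1–13 (diagnosis), 14–16 (follow-up), 17–20 (structure) and 21–23 (outcome): 13 + 3 + 4 + 3 = 23. This agrees with the Summary and section 7.1.

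**2. QI 21.** Taken literally, QI 21 = QI 16 and QI 19 and QI 21.

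- If QI 16 or QI 19 is not met, QI 21 is not met.
- If both are met, the rule reduces to QI 21 = QI 21. Pass and fail both satisfy it, so the text gives no answer.

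The alternative is QI 21 = QI 16 and QI 18 and QI 20. The sets {16, 19, 21} and {16, 18, 20} share only QI 16. A patient who meets 16, 18 and 20 but not 19 passes on one reading and fails on the other. A patient who fails QI 16 fails on both, so the ambiguity is active only where QI 16 is met. QI 16 applies only after a dementia diagnosis, and the appendix does not say whether QI 21 applies to an undiagnosed patient.

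**3. QI 22.** Most process indicators have an IF/THEN form that can be judged. QI 22 has no condition, threshold or direction, so no count can be converted into concordant or not concordant.

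**4. Weight in the score.** Assume equal weights and all 23 items applicable.

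- One item: 100/23 = 4.35 points.
- QIs 21 and 22: 2 × 100/23 = 8.7 points, leaving 21/23 = 91.3% of the score with a rule.
- Relative to the target: 8.7/22.5 = 39%.

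Each item adds between 0 and 4.35 points to an arm mean. The two together can therefore move the between-arm difference by anything from 0 to 8.7 points in either direction. The upper end needs the arms to differ completely on both items.

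Full applicability is a simplification. QIs 10, 13, 14, 15 and 16 require a dementia diagnosis and QI 22 concerns dementia patients. If such items drop out for an undiagnosed patient, 23 − 6 = 17 remain and one item weighs 100/17 = 5.9 points. Figure 2 likewise gives separate numbers for the diagnostic indicators (156) and the management indicators (about 50).

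**5. QI 16 against Appendix 1.** QI 16 asks for evaluation every 3 months, with updating only if needed. Appendix 1 asks for revision every 6 months, or sooner where required. QI 16 can be judged yes or no in both arms, and the allowance for earlier revision means that it can be met. A patient reviewed only at the 6-month default misses QI 16. Since QI 16 is in both readings of QI 21, that patient also misses QI 21: again 2/23 = 8.7 points for a patient to whom all items apply.

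**The case against.** The strongest reply is that the indicators come from a published validated set, and that the source or a statistical analysis plan may hold the missing rules. For QI 22 this has weight, since such a plan could state how the count is scored or reported. It does not remove the fault in the protocol, which places a raw count inside a percentage. For QI 21 the text is circular, which goes beyond being brief, and the authors' own question mark shows that it was not settled. The bracketed numbers look like an attempted renumbering, but that is a guess.

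Two stronger readings are tempting.

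- *Three indicators cannot be earned or scored.* A reader might add QI 16 and reach 3/23 = 13.0 points, or 13.0/22.5 = 58% of the target. The documents do not support this: QI 16 has a decidable rule, and Appendix 1 allows review before 6 months. Evaluation and revision are also not the same act.
- *The intervention is marked down by construction.* A reader might take the 49.1% diagnosed in the earlier trial cited in section 4.4 and compute 0.491 × 8.7 = 4.3 points lost (19% of 22.5). QI 16 is scored by the same rule in both arms, and section 5.1 says that usual care generally produces no comprehensive care plan, so most control patients would miss it too. A missed QI 16 records the care delivered, so it is not a bias. The rate also comes from outside this trial: Figure 2 plans about 50 of 156 = 32%, which on the same method gives 0.32 × 8.7 = 2.8 points. Neither number estimates a distortion of the treatment contrast.

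**Conclusion.** The point holds for QI 21 and QI 22. As written, the primary score cannot be computed for these two of 23 items without a decision that the protocol does not contain. QI 21 is the firmer error. Their share is 8.7 points of 100 with equal weights and all items applicable, against a target difference of 22.5. This is the part of the scale left undefined and a ceiling on what the choices could move. The actual effect is likely smaller, because QI 21 is ambiguous only where QI 16 is met, and the documents do not say how often that will be.

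For QI 16 the finding is narrower: the 3-month and 6-month passages do not agree and must be reconciled, and the mismatch carries into QI 21 under either reading. It does not show that QI 16 is unscorable or that the intervention arm is penalised. No sample-size or alpha figure depends on any of this.

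**What to change.** Before data extraction, and without knowledge of outcomes by arm:

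- **QI 21:** settle the component set against the source instrument and remove the self-reference. The bracketed set should not be adopted by default, since the authors queried it themselves. Alternatively, drop QI 21 from the total, because its components are already counted.
- **QI 22:** take it out of the percentage total and report it separately as a count by arm, with its denominator stated.
- **QI 16 and Appendix 1:** reconcile the two passages. No interval is proposed here.
- **Sensitivity analysis:** report the total with and without QIs 16 and 21.

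The cost is appendix wording. The downside is that the total then covers 22 items, or 21 if QI 21 is also dropped, and is slightly less comparable with the earlier 23-item score.
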